### Study eligibility and recruitment

The inclusion criteria for patients in this study are as follows: (i) patients with ACS who underwent percutaneous coronary angioplasty and inpatient CR, (ii) age ≥18 years at the time consent was obtained, (iii) inability to participate in outpatient CR after discharge, (iv) having a smartphone, and (v) agreeing to participate in this study after receiving verbal and written explanations from the researchers. Written consent was obtained from all participating patients in this study. The exclusion criteria are as follows: (i) lack of independence in activities of daily living, (ii) unstable angina, (iii) uncontrolled arrhythmia causing hemodynamic abnormalities, (iv) severe valvular disease, (v) uncontrolled diabetes, (vi) other diseases that contraindicate the use of exercise therapy, (vii) undergoing dialysis, (viii) other acute diseases or indications for surgical treatment, (ix) dementia, and (x) inability to make regular outpatient visits to the study site after discharge.

Researchers in Southern Tohoku General Hospital and Ohta Nishinouchi Hospital, which are the institutions conducting the study, will recruit study participants who have the potential to meet the eligibility criteria. The principal investigator of Fukushima Medical University, which is the institution responsible for the research, will oversee and manage patient enrollment.

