### Randomization and blinding

Randomization allocation will be performed on the web using the UMIN INDICE cloud (https://www.umin.ac.jp/indice/cloud.html). Allocation will be completed within 2 weeks of initiation of inpatient CR. This study will not be blinded. Adjustment factors for allocation will be age (<60 years *vs.* ≥60 years), sex (male *vs.* female), and highest creatine kinase level (<3,000 U/L *vs.* >3,000 U/L).

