### Online support for PA management

Patients in the intervention group will receive a wrist-worn wearable device (Fitbit Inspire 3, Fitbit, Inc, San Francisco, CA, USA) after assignment, and a web application (Recaval, SapplyM, Inc., Tokyo, Japan) for PA management will be downloaded to their smartphones. Data regarding PA and pulse rate obtained from the wearable device will be transmitted in real time *via* the application to the tablet device of the physical therapist in charge of the research facility. The wearable device is designed to locally store data until an internet connection is available. In addition to this biometric monitoring, the web application has chat and report feedback functions that allow two-way communication between patients and medical professionals. Patients will be instructed to wear the wearable device unless they are bathing or charging the device. Moreover, patients will be instructed to enter their daily blood pressure and self-records of subjective symptoms into the application, which will also be monitored daily by the physical therapist. Using this web application, patient information is completely anonymized; each patient is assigned a specific ID. In addition, this web application has a robust access restriction function. Only the interventionists at each research facility are only given access to the patient data of their own institution and have no access to the patient data of other research institutions.

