### Statistical analysis

In this study, the analysis will involve an intention to treat analysis. Therefore, patients’ consent will be obtained to use 3-month post-assessment information derived from the observed clinical data in the event of dropout or poor adherence in the intervention arm. Regarding background information of participants, discrete data, including frequencies, proportions, and 95% confidence intervals, will be calculated for each group. For continuous data, the mean, standard deviation, and 95% confidence interval will be calculated for each group.

The primary outcome, eGFRcys, will be examined using analysis of covariance (ANCOVA), with adjustment for baseline values as covariates for the least squares mean of eGFRcys at 3 months. Secondarily, between-group comparisons of the change in eGFRcys will be performed in the same way.

The secondary endpoints of ACR, BNP, average number of steps, peak VO2, and EQ-5D will be analyzed using ANCOVA, with adjustment for baseline values. Between-group comparisons of the incidence of adverse events will be performed using the *χ*-square test.

All statistical analyses will be performed using SPSS version 29.0 (IBM Corp., Armonk, NY, USA). Statistical significance will be set at an alpha-level of 0.05.

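### Two hospitals recruit, but site is in neither the stated allocation factors nor the stated ANCOVA models, so chance site imbalance and residual site differences stay in the treatment comparison; a site covariate removes this at almost no cost

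*Protocol article*

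**What the plan says.** Under Study eligibility and recruitment, the protocol article names two recruiting hospitals: "Researchers in Southern Tohoku General Hospital and Ohta Nishinouchi Hospital, which are the institutions conducting the study". It gives no target number per hospital.

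Under Randomization and blinding, allocation is web-based. The factors are listed with their cut-points: "Adjustment factors for allocation will be age (<60 years *vs.* ≥60 years), sex (male *vs.* female), and highest creatine kinase level". Hospital is not among them. The trial is open label: "This study will not be blinded".

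Under Statistical analysis, the primary outcome is compared by ANCOVA "with adjustment for baseline values as covariates for the least squares mean of eGFRcys at 3 months". The continuous secondary endpoints "will be analyzed using ANCOVA, with adjustment for baseline values". Neither model names site.

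Under Online support for PA management, the intervention is run locally. Wearable data go to "the tablet device of the physical therapist in charge of the research facility", and access is separated by hospital: "Only the interventionists at each research facility are only given access to the patient data of their own institution".

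**The concern.** Each hospital has its own therapists, physicians and exercise-test staff. The 3-month outcome may therefore differ between hospitals for reasons that the patient's baseline value does not capture. Possible sources include how usual care is given, how often patients take up outpatient rehabilitation (the Usual care section allows this in both arms), and how the exercise test is conducted.

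Randomisation that ignores hospital will, by chance, sometimes place more of one hospital's patients in one arm. Any remaining hospital difference then moves the treatment estimate in that trial, and the between-hospital variance sits in the error term. Both could be removed because hospital is known for every patient at entry. With 88 patients and a planned difference of 5 mL/min/1.73 m², it is worth knowing how large the effect could be.

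**Working it through.** **Inputs from the protocol article (Sample size calculation).** Total 88, 44 per arm; planned difference 5 mL/min/1.73 m²; SD 16.0; effect size f = 0.3125; alpha 0.05; power 0.80; 83 required before 5% dropout.

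**Assumptions, not in the documents.** Site split between 50:50 and about 70:30. Residual site difference after baseline adjustment of 0 to 8 mL, with 10 mL as a stress case. Correlation of 0.7 between baseline and 3-month eGFRcys. Allocation that ignores site.

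**1. The plan's own figure.** The ANCOVA F test with two groups and one covariate has 1 and N − 3 degrees of freedom and noncentrality f²N. At N = 83, f²N = 0.3125² × 83 = 8.105 and power is 0.803; at N = 82 it is 0.798. So 83 reproduces, and 83/0.95 = 87.4, which gives 88.

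**2. Chance imbalance in site share.** Let k be the number of hospital-A patients among the 44 in the intervention arm, when hospital A supplies s of the 88. Then k is hypergeometric, and the between-arm difference in site share is (2k − s)/44. At s = 44, Var(k) = 44 × 0.5 × 0.5 × 44/87 = 5.563, so SD(k) = 2.359 and the SD of the difference is 2 × 2.359/44 = 0.107.

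| Site split | SD of difference | P(≥10 points) | P(≥15 points) | P(≥20 points) |
|---|---|---|---|---|
| 44:44 | 0.107 | 29% | 13–14% | 5% |
| 53:35 | 0.105 | 38% | 19% | 8% |
| 58:30 | 0.102 | 26% | 11–12% | 4% |
| 62:26 | 0.098 | 24% | 10% | 3% |

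The higher 53:35 row reflects discreteness. With odd s the count difference is odd, and 9/44 = 20.5% just passes the threshold; with even s the first value past it is 10/44 = 22.7%. The SD is the steadier summary.

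**3. Shift in the estimate.** Shift = imbalance × residual site difference.

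| Residual site difference (assumed) | 1-SD imbalance (0.107) | 20-point imbalance |
|---|---|---|
| 0 mL | 0 | 0 |
| 3 mL | 0.32 mL | 0.6 mL |
| 5 mL | 0.54 mL | 1.0 mL |
| 8 mL | 0.86 mL | 1.6 mL |

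The largest entry, 1.6 mL, is 32% of the planned 5 mL (1.6/5).

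**4. Scale against sampling error.** With SD 16 and 44 per arm, the standard error of the difference is 16 × √(2/44) = 3.41 without credit for baseline. It is 3.41 × √(1 − 0.7²) = 2.44 with the assumed correlation. A shift of 0.54 mL is therefore about 0.16 to 0.22 standard errors.

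**5. Simulation (88 patients, 50:50 sites, 8,000 runs per scenario for site differences of 0, 3, 5 and 10 mL).** With site in neither allocation nor model, the mean estimate stayed at its true value and type I error was 0.049 to 0.055. The SD of the estimate was about 2.5 for site differences up to 5 mL. At 10 mL it was 2.65 to 2.70 without site and 2.46 to 2.48 with site in the model, and power for a 5 mL effect was 0.47 against 0.51. A further simulation gave 2.51 against 2.46 at 5 mL, and 2.62 against 2.46 at 8 mL.

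These simulated powers are well below 0.80 because the plan enters 5/16, a standardised mean difference, as f. For two equal groups f is half of that. This is a separate matter and does not affect the comparison with and without site.

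**6. Cost of the covariate.** On the plan's own inputs at N = 83, power is 0.8031 with the baseline covariate alone and 0.8030 with site added.

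**The case against.** Several counter-arguments stand.

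- **No bias.** A reader might infer that leaving site out biases the result or inflates the type I error. It does not. Allocation is still random, the estimate is correct on average, and the ordinary standard error already reflects chance imbalance.
- **No confounding of site with arm.** A reader might also infer that site and treatment effects could not be told apart in an imbalanced draw. Nothing in the article ties arm to hospital. At 60% against 40%, the arm-site correlation is about 0.2, so adjusting for site inflates the variance by 1/(1 − 0.04) = 1.04, or about 2% in the standard error.
- **Therapists are not the mechanism that adjustment repairs.** Local therapists coach the intervention arm only. Differences between them are a site-by-treatment interaction, which neither balancing nor a fixed site term removes.
- **No documented site difference.** The Usual care section does not say that care differs by hospital, and the article does not say where samples are assayed. The true residual difference could be zero, and the larger shifts combine an uncommon imbalance with an assumed input.
- **A fourth allocation factor is not free.** The article does not state the allocation method. If it uses stratified blocks, four binary factors give 16 cells, or 5.5 patients per cell.

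The omission itself remains. The article sets out both the allocation factors and the model covariates, and site is in neither list. A fuller plan that is not shown may include it; if so, the point is already met.

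**Conclusion.** The point holds as a modest one about precision and protection against chance imbalance. The plan is valid without site. Its estimate, however, is open to a shift in the realised trial of 0 to about 0.9 mL at a 1-SD imbalance, and 0 to 1.6 mL at a 20-point imbalance, against the planned 5 mL. These figures rest on the assumed residual site difference of 0 to 8 mL and on allocation that ignores site. The precision lost is small for site differences up to 5 mL and becomes visible only at about 8 to 10 mL. The recommendation rests on the near-zero cost of the remedy rather than on any demonstrated site effect.

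**What to change.** Before analysis, specify site (two levels) as a fixed covariate, alongside the baseline value, in the primary eGFRcys ANCOVA and in the secondary ANCOVAs. Apply it to all patients, including those already allocated. The cost is one degree of freedom per model, with no extra patients, visits or data.

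Adding site to the web allocation for patients still to be randomised is optional and not needed. If it is done, site must also be in the model: balancing on site without adjusting made the test conservative in simulation (type I error 0.036 at an assumed 10 mL site difference).

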### Intervention

Online support for PA management will begin at the time of discharge; additionally, patients in the intervention group will manage their own PA based on educational support provided by the physical therapist under the supervision of the primary physician (Fig. 2). The physical therapist administering the intervention must have ≥1 year of experience in physical therapy for patients with CVD, including ACS, or be a registered instructor of CR by the Japanese Association of Cardiac Rehabilitation (https://www.jacr.jp/en/).

**Figure 2 fig-2:**
[figure not shown]
Online support of physical activity management. Online support of PA management in this study will begin at the time of discharge from the hospital, and patients in the intervention group will manage their own PA based on educational support by the physical therapist under the supervision of the primary physician. PA, physical activity.

### Online support for PA management

Patients in the intervention group will receive a wrist-worn wearable device (Fitbit Inspire 3, Fitbit, Inc, San Francisco, CA, USA) after assignment, and a web application (Recaval, SapplyM, Inc., Tokyo, Japan) for PA management will be downloaded to their smartphones. Data regarding PA and pulse rate obtained from the wearable device will be transmitted in real time *via* the application to the tablet device of the physical therapist in charge of the research facility. The wearable device is designed to locally store data until an internet connection is available. In addition to this biometric monitoring, the web application has chat and report feedback functions that allow two-way communication between patients and medical professionals. Patients will be instructed to wear the wearable device unless they are bathing or charging the device. Moreover, patients will be instructed to enter their daily blood pressure and self-records of subjective symptoms into the application, which will also be monitored daily by the physical therapist. Using this web application, patient information is completely anonymized; each patient is assigned a specific ID. In addition, this web application has a robust access restriction function. Only the interventionists at each research facility are only given access to the patient data of their own institution and have no access to the patient data of other research institutions.

At the beginning of the intervention and at 2-week intervals thereafter, the physical therapist will provide the patient with a summary report of daily vital sign data, including educational comments and praise commending the achievement of PA and activity pulse rate goals, through the app. Regarding the target PA value, which is the basis of the educational support, the patients will be assigned a target of ≥5,000 daily steps, referring to a previously reported cutoff value for the number of steps per day that affects improvement of renal function in patients with ACS (Sato & Kohzuki, 2021; Sato et al., 2021). Further, this target can be achieved without worsening of vital signs or subjective symptoms. For example, if the weekly average daily step count is <5,000 steps/day, a smaller target of 1,000 steps/day is set for the next week and thereafter, which allows the patient to achieve the goal of ≥5,000 steps/day in incremental stages. As a safety management measure, the target values for pulse rate during activity and duration of activity above moderate intensity are set according to each patient’s results of the baseline cardiopulmonary exercise test and Karvonen’s formula (Makita et al., 2022). Table 1 shows the criteria for discontinuation of the intervention.

**Table 1 table-1:** Criteria for discontinuation of the intervention.

Criteria
(1) Cardiac arrest, severe bradycardia, fatal arrhythmia (ventricular tachycardia/ventricular fibrillation), or symptoms that cannot be ruled out during follow-up
(2) In case of sudden deterioration of vital signs or subjective symptoms (severe chest pain, abdominal pain, back pain, epileptic seizure, loss of consciousness, hypotension, severe joint pain, muscle pain, *etc*.).
(3) Accidents (falls, falls, bruises, trauma, *etc*.)
(4) In case of persistent hypertension (systolic blood pressure ≥ 250 mmHg or diastolic blood pressure ≥ 115 mmHg) or hypotension (systolic blood pressure < 80 mmHg) that is difficult to control.
(5) Deterioration of consciousness during follow-up
(6) The attending physician determines that the intervention should be discontinued due to changes in the patient’s condition or treatment strategy during follow-up
(7) The patient is hospitalized
(8) The patient wishes to discontinue the intervention.

Additionally, while monitoring daily PA, pulse rate, and self-recorded data regarding blood pressure, body weight, and subjective symptoms, the physical therapist will check the status and provide educational support for PA modification using the chat function of the application as required in case of the following scenarios:

 •The pulse rate during activity exceeds the target pulse rate by 20 beats/minute for >10 min •The pulse rate during PA falls below 50% of the target value for >5 consecutive days •The patient does not wear an activity monitor for >5 consecutive days •The patient’s self-recorded data indicate worsening subjective symptoms, including chest pain, shortness of breath, or fatigue •The patient’s has questions or complaints regarding PA management or disease management •The physiotherapist or physician in charge considered it necessary.

Furthermore, interviews will be conducted by telephone or *via* the ZOOM web conferencing service, as necessary.

### Usual care

All patients in both groups will receive usual care, including patient education, medications, outpatient visits, and laboratory tests upon discharge, within the relevant scope. However, if patients wish to participate in outpatient CR during the observation period, their wishes will be respected, and they will be allowed to participate in outpatient CR after consultation with their physician. In this case, the patient will not be excluded from the study and will continue to receive “intervention and outpatient CR” in the intervention group and “usual care and outpatient CR” in the control group.

### Outcome assessment

Table 2 describes the outcome measures for this trial. Patient characteristics and baseline measurements will be assessed at discharge (∼2 weeks after the onset of ACS) and reassessed after 3 months.

The primary outcome of this study will be the eGFR based on serum cystatin C (eGFRcys). In general clinical practice, the eGFR based on serum creatinine is widely used as an index for assessing renal function. However, PA, including exercise, can alter serum creatinine levels *via* changes in skeletal muscle mass. Therefore, cystatin C, which is independent of skeletal muscle mass, is preferred when examining the effects of PA on renal function (Séronie-Vivien et al., 2008; Poortmans et al., 2013). The eGFRcys will be estimated using the Japanese Society of Nephrology equation as follows:

eGFRcys (mL/min/1.73 m^2^) = 104  × Cystatin C^−1.019^ × 0.996^Age^ × 0.929 (if female)–8 (Horio et al., 2013).

This study will perform between-group comparisons of eGFRcys at 3 months adjusted for baseline values. eGFR decline after ACS may be particularly steep during the first 90 days after onset (Hillege et al., 2003). It is important to examine the inhibitory effect on eGFR decline during this period; accordingly, we set a 3-month follow-up period for this study. Most previous studies on the impact of outpatient CR on eGFR have similarly set a 3-month intervention and observation period (Toyama et al., 2010; Takaya et al., 2014; Hama et al., 2018; Sasamoto et al., 2021; Hama et al., 2022). Therefore, the follow-up period can be considered reasonable.

**Table 2 table-2:** All outcome measures and assessment schedule for this study. CPET, cardiopulmonary exercise test; EQ-5D-5L, Euro QOL 5-dimensions 5-levels; eGFRcreat, estimated glomerular filtration rate calculated from serum creatinine; eGFRcys, estimated glomerular filtration rate calculated from serum cystatin C; LPA, light-intensity physical activity; MPA, moderate-intensity physical activity; QOL, quality of life; SB, sedentary behavior; VPA, vigorous-intensity physical activity.

	Baseline	3-month
**Characteristics**: sex, age, alcohol consumption history, smoking history, location of coronary artery stenosis, Killip classification, contrast fee, medical history, comorbidities, echocardiography, length of hospital stay, height	•	
**Body conditions:** weight, body mass index, resting blood pressure, resting pulse rate	•	•
**Physical function:** CPET and grip strength	•	•
**Blood biochemical tests:** BNP, urea nitrogen, cystatin C, creatinine, glomerular filtration rate (eGFRcys and eGFRcreat), albumin, triglycerides, HDL-cholesterol, LDL-cholesterol, hemoglobin, blood sugar	•	•
**Urinalysis:** Urine albumin/creatinine ratio	•	•
**Physical activity:** step count, SB, LPA, MPA, VPA	•	•
**QOL**: EQ-5D-5L	•	•
**Medication**		
**Adverse events**		
(Intervention group only) ** Fitbit data:** daily sleep time and heart rate (maximum, minimum, and average)		

Secondary outcomes will include the urine albumin/creatinine ratio (ACR), BNP, average step count, peak oxygen uptake (VO2) based on a symptom-limited cardiopulmonary exercise test (CPET), Euro QOL 5-dimensions 5-levels, and incidence of adverse events. In addition, blood biochemical analysis data such as urea nitrogen; albumin; triglycerides; high- and low-density cholesterol; hemoglobin; and blood glucose will be collected. These outcome measures will be assessed concurrently with the primary evaluation. In the symptom-limited CPET, to avoid overloading the cardiovascular system after ACS, the exercise load is terminated when the gas exchange ratio reaches 1.2, which is defined as the peak point, even before reaching the symptom limit (Sato et al., 2023).

PA assessment will be performed immediately after discharge and after 3 months for a 7-day period. The Active Style Pro HJA-750 (Omron Healthcare Company; Kyoto, Japan), which has a 3-axis accelerometer that has been validated and shown to be highly reliable (Oshima et al., 2010; Ohkawara et al., 2011), will be used to evaluate PA and the average number of steps. Sedentary behavior, light-intensity PA, moderate-intensity PA, and vigorous-intensity PA will be defined as PA of ≤1.5 metabolic equivalents (METs), >1.5 and <3.0 METs, ≥3.0 and <6.0 METs, and >6.0 METs, respectively (Bull et al., 2020); moreover, the time spent wearing the device will be collected. To avoid the impact of checking PA on increasing PA levels, the researcher sets the device to prevent displaying the PA data. The patients will be instructed to wear the accelerometer at all times except when sleeping and bathing. If the time the device is worn is <10 h per day, activity data for that day will be excluded. The minimum number of days required for evaluation is defined as “4 days or more”, which is more than half of the 7 days (Fig. 3). Patients will return the accelerometer to the hospital by mail at the end of that 7-day PA measurement period. The principal investigator at each hospital will transfer PA data from the accelerometer to the computer *via* a reader (HHX-IT4, Omron Healthcare Company; Kyoto, Japan).

